## **10.5 Safety and monitoring during intervention period for both study arms**

### **10.5.1 Monitoring for fluid overload**

Participants in both arms of the study will be **monitored for signs of fluid overload**, and fluid administration ceased or reduced based upon clinical assessment by the treating clinician. Signs of fluid overload include peripheral oedema, increased bilateral inspiratory auscultatory crackles, and radiographic evidence of pulmonary oedema.

### **10.5.2 Monitoring for hypovolaemia or hypoperfusion**

Participants in both study arms will be **monitored for signs of hypovolaemia or hypoperfusion** and managed with additional IV fluids in accordance with the trial protocol. If a participant develops evidence of central (e.g. bowel) or peripheral (limb or digit) ischaemia or mottling, treat accordingly and continue the protocol where clinically appropriate. Signs of hypovolaemia or hypoperfusion may include persistent tachycardia, altered mentation, reduced capillary refill time and oliguria.

## **10.6 Ancillary treatments**

All patients will receive additional treatment for sepsis according to clinician discretion and the SSC guidelines including airway and ventilator management, early broad-spectrum antimicrobial agents and source control where required. All patients will be managed initially in a critical care ward (ED, ICU, HDU) until their condition stabilises. The type of fluid administered and the use of therapies such as inotropic agents or corticosteroids will be at senior treating clinician discretion. To avoid unnecessary placement of a CVC, peripheral IV administration of vasopressors for up to 24 hours in accordance with local policies and guidelines is permitted.

Physiological and laboratory data will be collected where this is available as part of usual care. No additional blood tests or procedures are required for study purposes.

### **10.7 Disposition**

We expect that the majority of participants in the trial will be admitted to ICU or HDU from the ED. In keeping with the pragmatic nature of the trial, the ultimate decision about admission disposition will be at the discretion of the treating clinicians.

### **10.8 Discontinuation of treatment**

The trial intervention arms will be continued for at least the first six hours post-randomisation. For those admitted to ICU the interventions will continue up to 24 hours post-randomisation, or until transfer to a general ward, whichever occurs first. Following cessation of the study intervention, haemodynamic management will be according to usual practice.

### **10.9 Follow up at day 90, 6 and 12 months**

The descriptor for the person who is legally allowed to give consent will vary between jurisdictions. For the purposes of this protocol, the descriptor 'legally authorised representative' (LAR) describes the person who is legally allowed to give consent for the participant.

The participant or a LAR, if the participant has not regained capacity, will be contacted via a telephone call at 90 days, 6 and 12 months after randomisation for study follow up.

The day 90 follow up will be to establish survival at this time point and additionally to collect important information on readmissions and discharge to other hospitals, rehabilitation hospitals or long term nursing care facilities. This will inform the primary outcome for the study. As this information will be collected from the participant or (LAR), a diary/information collection sheet will be provided prior to hospital discharge to assist with this information collection.

At 6 and 12 months after randomisation, the participant or LAR will be contacted again via a phone call. This call will collect information quality of life and functional outcome information by the E-Q-5D and WHODAS 2.0 surveys.

### **10.10 Bias Minimisation**

Given the nature of the intervention, it is impossible to blind treating clinicians and participants for logistical and safety reasons. Study treatment assignment will be revealed to treating staff as they are required to apply their clinical judgement in the delivery of the trial protocol.

Bias will be minimised by:

1. ensuring concealment of the treatment allocation until completion of the randomisation procedure
2. regular monitoring and reporting of protocol compliance and

3. an objective primary outcome measure which is not susceptible to ascertainment bias.

## 11.ETHICS

### 11.1 Ethical conduct of the study

This study is to be performed in accordance with the ethical principles of the Declaration of Helsinki (June 1964 and amended 1975, 1983, 1989, 1996, 2000, 2008 and Note of Clarification 2002 and 2004), ICH GCP Notes for Guidance on Good Clinical Practice (CPMP/ICH/135/95) E6(R2) annotated with Therapeutic Goods Administration comments, NHMRC National Statement on Ethical Conduct in Research Involving Humans 2007 (Updated 2018), the New Zealand Interim Good Clinical Research Practice Guidelines (Volume 2 1998 and Volume 3 2000).

Ethics approval will be obtained from all relevant ethics committees in each jurisdiction/country that is participating. Each participating site will submit the protocol and other relevant study documentation to the responsible local governance office for site-specific assessment. Approval of the protocol and related documents will be obtained prior to the start of the study. It is the principal investigators responsibility to ensure that all conditions for approval of the study are met and that amendments to the protocol or serious adverse events are also reported to the HREC as required by that committee. The inclusion in the trial of adults with incapacity to consent will be governed in accordance with the legal jurisdiction of each participating site.

### 11.2 Ethical considerations of the study

The ethical considerations of this study are:

- The risk/benefit ratio of the study treatment.
- Data protection and confidentiality of participant data.
- The enrolment of participants who are unable to consent for themselves

### 11.3 The trial compares two standard care treatment arms

Our observational study demonstrated variation in haemodynamic resuscitation practice among participants with septic shock among Australian and New Zealand EDs ranging between a fluid restricted and early vasopressor strategy and a liberal fluid and later vasopressor approach. The resuscitation regimens in the two arms of this trial *encompass this range of usual care*, and this trial is therefore comparing the effectiveness of these two strategies accepted by substantial numbers of medical practitioners specialising in the area of practice concerned. Participants in both arms of the trial will therefore be receiving treatment within the bounds of accepted standard clinical practice with no components of care being new or experimental. The treating clinician is expected to have equipoise about which of the two treatment strategies to employ in order to enrol a participant into the trial. A clinical contraindication to employing either or both of the treatment strategies is an explicit exclusion criterion. Regardless of the treatment arm, and, because the trial is unblinded, the treating doctor retains ultimate control over the volume of resuscitation fluid and the timing of vasopressors within the

parameters recommended in the study protocol. The treating doctor may deviate from the treatment protocol if deemed to be in the interest of the participant (with the reasons for this documented in the case report form). Thus, participants in the trial are considered to be at no greater risk than if they were receiving treatment outside the trial. Thus the risk/benefit ratio of the trial where both trial arms are encompassed by the range of usual care and is accepted as such by medical practitioners specialising in the area of emergency medicine and intensive care in Australia and New Zealand confers no greater clinical risk than receiving routine treatment.

### ***11.3.1 With regards to the NSW Guardianship Act.***

Acknowledging advice from the Civil and Administrative Tribunal of NSW in the case of *Shehabi v Attorney General (NSW)* [2016] NSWCATAP 137 [37], we note that the tribunal defines a clinical trial for the purposes of the Guardianship Act 1987 (NSW), s 33(1) as “a trial of drugs or techniques that necessarily involves the carrying out of new medical or dental treatment that has not yet gained the support of a substantial number of medical practitioners or dentists specialising in the area of practice concerned.” The ARISE-FLUIDS trial will compare two resuscitation strategies that use intravenous fluids and vasopressors for the resuscitation of patients with early septic shock. Intravenous fluids and vasopressors used are well established treatments for patients with early septic shock [38,39]. These treatments are supported by the majority of practitioners in the field, as evidenced by observational studies,[38,39] as well as being recommended by the NSW Clinical Excellence Commission Sepsis Pathway [40]. Given that the treatments administered in the ARISE-FLUIDS trial are not new treatments and they are widely accepted by the majority of practitioners specialising in the area of practice concerned, we submit that the ARISE FLUIDS trial does not meet the established criteria to be considered a clinical trial according to the NSW Guardianship Act 1987 (NSW), s 33(1).

### ***11.4 Data protection and confidentiality of patient data***

All investigators and research staff will comply with the legislative requirements of their jurisdiction with regard to the collection, storage, processing and disclosure of personal information. Confidentiality of all participant data will be maintained by the use of unique identifiers, password protected electronic databases, secure storage of records and precautions to control access to authorised personnel only. All records will be kept in compliance with local ethical and research governance policies.

Participants will be randomised via a secure database and allocated a unique study number. The site research coordinator will compile an enrolment log which contains identifying information. Subsequent data will be identified by the unique study number only. The enrolment log and study data will be kept separately. Follow-up details of the participant and their LAR (if the participant has not regained adequate capacity) will be collected for the 6- and 12- month outcome assessment conducted via telephone including name, address and contact telephone numbers/email. These contact details will be kept confidentially at the site in a locked filing cabinet in the research office and will not be accessible outside the research team of the recruiting hospital.

### ***11.5 The enrolment of participants who are unable to consent for themselves***

Who may give consent for a patient to take part in medical research will vary between legal jurisdictions according to their local legislation. Each site's Principal Investigator is responsible for ensuring that the relevant local legal requirements are followed. The term used to describe the person who may give consent for a patient to take part in medical research will also vary between jurisdictions. For the purposes of this protocol, the descriptor 'legally authorised representative' describes the person who is legally allowed to give consent for the participant.

All interaction between research staff and participants and their relatives will take into consideration the stress or emotional factors associated with critical illness and ensure that the dependency of potential participants and their relatives on medical personnel providing treatment does not compromise the freedom of a decision to participate. Consenting to participation will be voluntary and participants or their legally authorised representative (LAR) will be free to withdraw from participation at any time without giving reasons.

#### ***11.5.1 Urgent treatment for septic shock and trial inclusion unable to be separated***

Due to the critical nature of septic shock, treatment needs to be commenced rapidly under emergency conditions and is part of life-saving care. Additionally, the study treatment arms, both which encompass standard care for septic shock, cannot be separated from life saving care.

#### ***11.5.2 Unable to obtain patient or LAR consent prior to enrolment***

The patient with septic shock is critically ill, requires time critical care and due to their condition is unable to provide valid and reliable consent. The patient's legally authorised representative (LAR) is often not present at this time or in many cases is not known or contactable. If, however, the LAR were present or contactable, taking into consideration the stress and emotional factors involved it would not be practical, nor feasible to obtain an informed consent in a respectful manner. The burden of this situation would be unfair to the LAR as detailed in the National Statement on Ethical Conduct in Human Research 2007 (updated 2018) section 4.4.11 [41].

#### ***11.5.3 Enrolment without prior consent***

In view of the above, we will seek approval for enrolment without prior consent where this is consistent with local jurisdictional requirements and legislation. This approach is in line with the principles in paragraph 4.4.13 of the National Statement on Ethical Conduct in Human Research and is justified on the basis that the trial is *comparing the effectiveness of two accepted treatment strategies and trial participation confers no greater clinical risk than receiving routine treatment, as detailed in protocol section 11.3.*

Enrolment will only occur provided the following conditions are met:

- The patient's condition requires urgent treatment which cannot be delayed
- The patient meets all trial eligibility criteria with no exclusions

- It is not possible to obtain an informed, respectful consent from the legally authorised representative without delaying treatment
- The research project is not contrary to the interests of the patient.

These above conditions will be documented in the medical record.

### ***11.6 Informed consent procedures- Australian context***

As soon as reasonably practicable following recruitment, the LAR and/or the participant will be informed of the participant's inclusion in the trial. The study treatment period for the trial is limited i.e most participants will have completed all active treatment within 6 hours of randomisation. A smaller number of participants may receive active study treatment for up to a maximum of 24 hours. Therefore, the consent will be for the use of study data and follow up.

Dependent on local jurisdictional requirements and legislation, this trial will employ either one of the following 2 approaches:

- Opt-out
- Consent to continue

#### ***11.6.1 Opt-out approach***

Subject to local HREC approval and where opt-out approach to consent is consistent with local jurisdictional requirements and legislation, we will request an opt-out approach for use of data and follow up. We believe the conditions for this opt-out approach as described in the National Statement 2.3.5 and 2.3.6 have been met in the ARISE Fluids trial. Refer to Appendix 1 for the National Statement 2.3.6 opt-out approach criteria and the trial's specific meeting of these conditions. Given our experience with trials in critically ill patients and from our consumer representative advice, when a waiver for enrolment has been granted, participants and LARs often find it confusing to provide written consent for data when the research treatment procedures have already taken place and they frequently perceive that more research specific interventional procedures are required.

Where an opt-out approach is approved, the site Principal Investigator, or their nominated delegate, will provide a plain language information sheet and brochure to the participant and/or LAR at the earliest appropriate opportunity. The information sheet and brochure will explain all aspects of the trial and the procedure to decline or opt-out from data collection and follow up. Additional to this written information, the site Principal Investigator, or their nominated delegate, will provide a verbal explanation of the trial and the opportunity to ask questions and have these answered. This combined process of both written information and verbal exchange will constitute an overall process to facilitate participant/LAR understanding of the information. It will also provide the best opportunity for the participant/LAR's understanding of the information to be demonstrated to the research member undertaking the opt-out approach. This information sheet and brochure will detail the process for declining or opting out of study participation. They will be given the information sheet and brochure

to keep and may seek further information or opt-out at anytime. The provision of the opt-out information sheet and brochure to the LAR/participant will be documented in the medical record and a copy of the information sheet and brochure will be placed in the participant's medical record. If the LAR or participant decides to opt-out of the trial this will be clearly documented in the medical record.

#### ***11.6.2 Consent to Continue***

Subject to local HREC approval, and where opt-out consent is not consistent with local jurisdictional requirements and legislation, we will seek consent to continue participation in the trial. The site Principal Investigator, or their nominated delegate, will provide a plain language information sheet and consent form to the participant and/or LAR at the earliest appropriate opportunity. The information sheet will explain all aspects of the trial and the ability to decline or withdraw from data collection and follow up. Additional to this written information, the site Principal Investigator, or their nominated delegate, will provide a verbal explanation of the trial and the opportunity to ask questions and have these answered. This combined process of both written information and verbal exchange will constitute an overall process to facilitate participant/LAR understanding of the information. It will also provide the best opportunity for the participant/LAR's understanding of the information to be demonstrated to the research member undertaking the consent to continue. They will be given the information and consent form to keep and may seek further information or withdraw at anytime. The consent process will be documented in the medical record and a copy of the information and consent form will be placed in the participant's medical record.

#### ***11.6.3 Deceased patients***

Participants enrolled in this study have septic shock and consequently the participant may deteriorate rapidly and unexpectedly. In the circumstance where a participant enrolled in the study under the process explained in 11.6.1 & 11.6.2 above, dies before consent has been obtained, we will use participants' data for the study. All attempts to contact the family and relevant circumstances prior to the death of any participant will be documented in the medical record. To seek consent from grieving family members would be stressful and inappropriate. Additionally, the study integrity and safety data would be compromised without this data.

#### ***11.6.4 Informed consent cannot be obtained from the participant or legally authorised representative***

There may be the circumstance where a participants never regains competence following enrolment into the trial under the process explained in 11.6.2 above and there is no legally authorised representative available. If the participant is under a Guardianship Order then consent will be sought following the legislation and processes in place in that jurisdiction as long as the Guardianship Order includes consent to medical treatment. In the circumstance of a participant who never gains capacity and there is no LAR or a Guardianship Order which does not include decisions on consent to medical treatment, an approach will be made to the relevant HREC to request that study data may be retained and used.

### **11.7 Informed consent procedures- New Zealand context**

In New Zealand, the approach used will be consistent with Right 7.4 of the Health and Disability Code [42], which outlines the framework for providing treatment to participants who are unable to consent for themselves. Consent will be in line with section 11.6.2 Consent to Continue with the addition of the specific approach detailed below.

The specific approach will be:

1. To consider whether the study assigned administration method and study participation is in the best interest of each individual patient, and
2. As soon as it is practical and reasonable, to seek the advice of persons interested in the participant's welfare to establish that study participation is consistent with the participant's wishes.

All participants who recover sufficiently will be given the opportunity to provide informed consent for ongoing study participation and for the use of data collected for the study.

## **12.DATA MANAGEMENT**

### **12.1 Data collection and management methods**

Data collection will be restricted to those variables necessary to define baseline participant characteristics, the delivery of the intervention in both arms, potential confounding co-interventions, and outcomes.

All data will be collected by trained research staff at each participating site; the paper case report form (CRF) worksheet may be used to collect the data from the medical record. Each participant will be assigned a unique study number at randomisation and only non-identifying data will then be entered into a web database (electronic case record form [eCRF]) by the site research staff. Data queries will be automatically generated via the electronic data collection database.

Randomised participants will be followed up until death or 90 days post-randomisation whichever occurs first for the primary outcome and thereafter up to 12 months for secondary outcomes. Follow up will be performed by site study staff by either direct contact with the participant or their LAR (if the participant has not regained adequate capacity). In all cases where the participant regains capacity they will be responsible for the provision of their own data. References to the LAR is only relevant where the participant has not regained capacity. Full protocol data will be collected for all randomised participants. If consent for participation is withdrawn or if the participant or LAR wish to opt-out, data will not be included unless consent to do so is obtained.

Participants and/or their LAR will be asked to provide three possible points of contact (home and close family contact details) to the research staff prior to discharge. Participants (or a LAR proxy) who are alive at 6 and 12 months after randomisation will be contacted by the site research coordinator via telephone. If it is not possible to contact the participant or LAR on the telephone, a copy of the relevant questionnaires will be sent to them via post or email. If the questionnaires are completed at home a return address, stamped-addressed envelope

will be provided. The research coordinators will administer, or the participants or LAR will complete, the WHODAS functional status assessment and EQ-5D-5L quality of life assessment.

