## **13. STATISTICAL CONSIDERATIONS**

Participants who do not receive the allocated intervention according to the parameters set in the allocated study arm will be analysed according to the allocated arm according to the intention to treat principle.

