### **13.2 Statistical and analytical plan**

The primary outcome (DAOH-D90) and other non-parametric outcomes will be analysed using quantile regression with results presented as median difference (95%CI). Mortality and other binomial outcomes will be analysed using logistic regression with results reported as odds ratios (95%CI). Time to event outcomes will be analysed using proportional hazards regression with results presented as Kaplan Meier or cumulative incidence curves where mortality is a competing risk. Functional status and quality of life will employ longitudinal analysis techniques to account for data collected at both 6 and 12 months. All analyses will account for site with participants nested within site and site treated as a random effect. Where baseline imbalance ( $p < 0.2$ ) is observed between treatment arms, sensitivity analysis will be performed adjusting for imbalanced variables. Sensitivity to missingness will be performed using multiple imputation. A secondary analysis will be conducted using a Bayesian approach to model a posterior probability of the odds ratio for days alive and out of hospital at 90

days post-randomisation between the intervention and control group with associated 95% credible interval (CrI). Statistical analysis will be performed using SAS or R and a detailed statistical analysis plan will be published or posted in the public domain prior to study completion.

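### Whether a randomised participant's data stay in the analysis depends on being alive when consent is sought: earlier deaths are always kept, living decliners are removed unless they agree to data use

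*Protocol*

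**What the plan says.** Sections 11.5.3 and 11.6 provide for enrolment without prior consent. The participant or legally authorised representative (LAR) is told later, and what is then sought covers use of data and follow-up. Section 10.10 states that treatment is not blinded.

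Four rules then decide whose data are used:

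- Section 11.6.3, for a participant who "dies before consent has been obtained, we will use participants' data for the study".
- Section 12.1, on withdrawal or opt-out: "if the participant or LAR wish to opt-out, data will not be included unless consent to do so is obtained".
- Section 11.6.1, on timing: participants and LARs "may seek further information or opt-out at anytime".
- Section 11.6.4, for a participant who never regains capacity and has no LAR able to decide: "an approach will be made to the relevant HREC to request that study data may be retained and used".

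In the same paragraph as the exclusion rule, section 12.1 also says: "Full protocol data will be collected for all randomised participants". Section 13 says that participants not treated as allocated "will be analysed according to the allocated arm according to the intention to treat principle", and the synopsis describes the outcome analysis as intention to treat. On missing data, section 13.2 says: "Sensitivity to missingness will be performed using multiple imputation".

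**The concern.** Membership of the analysis set should not depend on anything that happens after randomisation and is tied to the outcome. Here it does. A participant who dies before the approach cannot be removed; a participant who lives to be approached can be. Under section 8.1, death by day 90 scores zero, so the records protected from removal are zeros, while the removable ones come from a group with a higher average score.

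The decision is also taken when allocation is no longer concealed. Experience of the assigned strategy, or the way staff describe it, could make opt-out differ between arms. Section 10.10 relies on an objective primary outcome to limit bias, but objective measurement does not protect against selective removal of records.

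The outcomes at stake are DAOH-D90 and 90-day mortality, the first secondary outcome. The protocol sees the danger on one side: 11.6.3 justifies keeping deaths on grounds of study integrity, and Appendix 1 item (c) rests the opt-out approach on the need for near-complete participation.

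**Working it through.** **Sample size, reproduced first.** Inputs from 13.1: SD 31, difference 7, power 90%, alpha 0.05 (two-sided reproduces the figure). Per arm, n = 2 × 31² × (1.960 + 1.282)² / 7², which rounds up to 413, or 826 in total. Then 826 × 1.15 = 949.9, stated as 950, and 950 / 0.95 = 1000. The sample size is sound. Its 5% drop-out allowance protects precision only and does nothing about selective removal.

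**Inputs for the bias check**

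- Mean DAOH-D90 of 60 days (13.1), the same in both arms, so no true effect.
- Mortality m: 8% (section 6, observational study, septic shock) and 22% (section 6, ICU sepsis with shock). Both are in-hospital figures, used as a range for 90-day mortality.
- Opt-out fraction w among those alive at approach: not in the protocol; assumed 0% to 10%, and random among the living.
- Share of deaths before the approach, e: not in the protocol; assumed 100%, 50% or 0%.

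**Formulas**

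- Survivor mean = 60 / (1 − m).
- Fraction of the arm removed = w(1 − m·e).
- Retained mean = 60(1 − w) / [1 − w(1 − m·e)].
- With e = 1, apparent mortality = m / [1 − w(1 − m)].

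**Equal opt-out, 5% in both arms, e = 1**

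- m = 22%: mean 57 / 0.961 = 59.3 and mortality 0.22 / 0.961 = 22.9%, in each arm.
- m = 8%: mean 57 / 0.954 = 59.7 and mortality 0.08 / 0.954 = 8.4%, in each arm.
- The between-arm difference is 0. Levels shift; the comparison does not.

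**Unequal opt-out, e = 1**

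| Opt-out | m | Retained means | False difference | Apparent mortality |
|---|---|---|---|---|
| 2% v 8% | 22% | 58.8/0.9844 = 59.73 v 55.2/0.9376 = 58.87 | 0.86 days | 22.3% v 23.5% |
| 2% v 8% | 8% | 58.8/0.9816 = 59.90 v 55.2/0.9264 = 59.59 | 0.32 days | 8.1% v 8.6% |
| 0% v 10% | 22% | 60.00 v 54/0.922 = 58.57 | 1.43 days | 22.0% v 23.9% |
| 0% v 10% | 8% | 60.00 v 54/0.908 = 59.47 | 0.53 days | 8.0% v 8.8% |

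**Fewer deaths before the approach, 2% v 8%.** With e = 50%, the difference is 0.43 days at m = 22% and 0.16 days at m = 8%. With e = 0 it is zero, because opt-out then removes later deaths and survivors in proportion.

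**Median, the planned estimate in 13.2.** A simulation used 22% mortality, e = 1 and a right-skewed hospital stay (log-normal, median 9.5 days, log-SD 0.85); it gave mean 59.7 and SD 33.7. The retained median is 76.99 at 2% opt-out and 76.70 at 8%, a shift of about 0.3 days. For 0% v 10% it is 77.08 v 76.60, about 0.5 days.

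**If there is a true effect.** With mortality of 18% v 22%, the same survivor mean and 5% opt-out in both arms, a true difference of 3.08 days is observed as 3.17. Equal opt-out then distorts the comparison only slightly.

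**The case against.** Several points against a stronger reading stand.

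- **Survivors only.** A reader might infer that the rule removes only day-90 survivors. It does not. It removes people alive when they or their LAR decline, which may be at any time, and some of them will die before day 90. Their zeros are removed too.
- **Loss to follow-up.** A reader might add that people lost after discharge are all survivors. Leaving hospital alive is not survival to day 90. The protocol also excludes people who cannot be followed (9.4), asks for three contact points (12.1), provides a diary (10.9) and records vital status at days 28 and 90 (12.2).
- **Automatic removal.** Section 12.1 already allows data to stay with consent, and 11.6.4 gives a limited route through the ethics committee.
- **Multiple imputation cannot repair it.** Section 13.2 names no missing-at-random assumption and no imputation variables, and does not say whether opt-outs are included. That detail may properly sit in the SAP. A wholly removed record does leave little to impute from, and a model that ignored being alive at opt-out would impute too many deaths, but the protocol does not say that this will be done.
- **Intention to treat.** The sentence in section 13 concerns participants not treated as allocated. It makes no explicit promise about people who refuse data use, so the tension is with the label in general.
- **Size.** The opt-out splits are assumptions. The largest 2% v 8% figure, 0.86 days, is under half the standard error of a mean difference: 31 × √(2/500) = 1.96.

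These points narrow the claim. They leave the asymmetry between 11.6.3 and 12.1 and the conflict inside 12.1. Nor could a SAP recover data that the consent process never asked permission to keep.

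**Conclusion.** The concern holds in a limited form. Sections 11.6.3 and 12.1 together make retention depend on being alive at the approach, after open-label allocation. Since 11.6.1 lets people opt out of data collection itself, full data on everyone randomised cannot be guaranteed as 12.1 states.

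The effect is lower DAOH-D90 and higher apparent mortality in any arm with opt-outs. With no true effect, the comparison is biased only if opt-out differs by arm. At 2% v 8%, with all deaths before the approach, the false mean difference is 0.32 to 0.86 days at 8% to 22% mortality, or about 5% to 12% of the 7-day target. The median shift is about 0.3 days at 22% mortality. Mortality differs falsely by about 0.5 to 1.1 percentage points (0.08/0.9264 − 0.08/0.9816 and 0.22/0.9376 − 0.22/0.9844). The mean differences roughly halve if half of deaths come first.

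All this assumes that opt-out is random among the living; opt-out related to recovery could make the bias larger or smaller. The documents do not support reading this as a demonstrated bias in the treatment effect. It is a modest, avoidable exposure.

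**What to change.** In 11.6 and 12.1, replace the all-or-nothing exclusion with a tiered opt-out, subject to ethics approval and local law:

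1. stop further contact;
2. separately, permission to keep data already collected;
3. separately, permission to take vital status and hospital admission dates to day 90 from records.

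Reword 12.1 so that the full-data sentence and the exclusion rule agree with each other and with 11.6.3, and state how full removals fit the intention-to-treat set.

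Report the number of full removals by arm. Add a sensitivity analysis of DAOH-D90 and 90-day mortality that restores each fully removed participant to the allocated arm as alive at opt-out, over a range of low to high DAOH. The low end should allow for death after opt-out.

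The cost is information-sheet wording, its ethics review and one extra analysis. The sample size stays at 1000. Some participants will still refuse all use of their data, so the exposure is reduced and bounded but not removed.
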